### PRS supervision

2.10

The approach to supervision includes both PRS supervision led by a PRS supervisor and clinical supervision led by a clinical psychologist. Weekly supervision sessions with a PRS supervisor include real-time case reviews of participant sessions where the PRS interventionist can raise questions and seek guidance, and the PRS supervisor can assess PRS performance in the intervention administration after listening to session recordings for fidelity monitoring. Based on these discussions, the PRS supervisor reviews relevant content and provides ongoing training to the PRS interventionist and supports resource brokering to ensure the PRS interventionist can refer participants to various community resources, as needed. PRS supervision sessions equally focus on knowledge-building and skills development with the goal of enhancing the understanding of systems of care, pathways for MOUD, the goals and agenda of MOUD care, person-centered support, and reducing barriers to receiving care. Additionally, PRS interventionists engage in twice weekly check-ins, ranging from 30- to 60 min in length, as required, to address real-time developments in training and delivery of the intervention, including regular monitoring of session fidelity as well as one’s own recovery and self-care. The PRS supervisor and PRS interventionists also consult on a weekly basis with clinical psychologists on the team to refer for higher level clinical needs and referrals, as well as to preserve role boundaries for PRSs and have sufficient support from licensed mental health clinicians. Clinical psychologists are also available to support ongoing booster training needs for BA and problem solving skills.

### Follow-up assessments

2.11

Participants from both study groups (PA + TAU and TAU) complete follow-up assessments: post-core intervention sessions follow-up (PCFU) approximately six to 12 weeks post baseline and final follow-up (FFU) approximately 18–24 weeks post baseline. Follow up assessments are conducted by an independent blinded assessor who is trained on all study procedures but outside the core study team and blinded on randomization status. Measures administered are similar to the baseline assessment (see Table 1). Intervention implementation measures are completed during the PCFU assessment by an unblinded research team member and assess feasibility, acceptability, and fidelity among participants who received the *Peer Activate* intervention.

### Effectiveness outcomes

2.12

#### Primary outcomes

2.12.1

##### Methadone treatment retention

2.12.1.1

The primary effectiveness outcome for this trial is methadone treatment retention, which is assessed over six months post baseline. Methadone treatment retention is examined through clinical records of appointment attendance and determined based on one or more methadone treatment-related visit(s) attended for each 30-day period during the six months following baseline. The primary outcome is retention assessed dichotomously (i.e., yes/no) at approximately six months post baseline. Participants who are referred to another internal treatment program or transferred to an external methadone treatment program are considered retained at six months based on clinic-verified records. To supplement the dichotomous measure of retention, we will also assess methadone treatment persistence, defined as the proportion retained on methadone treatment monthly over six months (i.e., at least one methadone dose for each 30-day period) post baseline, and days retained in treatment.

#### Secondary outcomes

2.12.2

We will also assess methadone treatment retention and persistence at three months post baseline, as well as changes in substance use over six months using both urinalysis and timeline follow back methods and depressive symptoms using the PHQ-8. For implementation outcomes, we will assess adoption of the intervention qualitatively through focus groups with providers and other key stakeholders (*n* = 12) about intentions to implement the intervention following the trial and to inform future adaptations to *Peer Activate* and plans for adoption and sustainability. Focus groups will be led with a semi-structured guide using Proctor’s model to define adoption (41).

#### Implementation outcomes

2.12.3

Implementation outcomes were defined based on Proctor’s model (41), including feasibility, acceptability, and fidelity, using mixed methods as detailed below.

##### Feasibility and acceptability

2.12.3.1

Feasibility and acceptability are assessed by session attendance (both initiation of the intervention and attendance at core sessions, respectively, See Table 1) and using a validated quantitative measure of feasibility and acceptability, the Applied Mental Health Research Group implementation outcome assessment (48). This assessment has been used to evaluate the implementation of interventions delivered by peer and lay health workers internationally and was designed to be adaptable for use in different resource-constrained settings globally (34, 49). In addition to quantitative measures, we are collecting qualitative feedback from patients (interviews offered to *Peer Activate* participants demonstrating either high treatment adherence or challenges with treatment during study engagement; *n* = 40) about their experiences with the intervention with specific probes related to feasibility and acceptability based on Proctor’s definitions (41). Qualitative and quantitative measures of feasibility are assessed at the posttreatment follow-up assessment (approximately three months post-baseline) or in the event of early participant discontinuation of the study.

##### Intervention fidelity

2.12.3.2

All *Peer Activate* sessions are audiotaped with patient permission as part of the consent process, and a randomly selected 20% are reviewed by a trained, independent rater, assessing both adherence and competence (50). The PRSs also self-report intervention adherence following each session. An adapted rating checklist for PRS adherence is utilized to determine whether the specific treatment components were delivered (both PRS report and independent ratings). Following recommendations for implementation science research (51), a “fidelity score” is calculated based on the proportion of key intervention components delivered as intended across sessions. Competence in the domain of general clinical skills (e.g., empathic listening, non-judgment) is rated using the ENhancing Assessment of Common Therapeutic Factors (ENACT) rating scale (52), a cross-cultural competency measure of skills of lay counselors, including PRSs specifically, in delivering a behavioral intervention. Prior research has seldom captured how to balance delivery of an evidence-based intervention, such as BA, with sharing one’s own identity as a PRS or adhering to the PRS role. The combination of these fidelity measures allows us to capture these unique elements of a PRS-delivered intervention (25).

### Retention of study participants

2.13

As a strategy to support retention in a traditionally hard-to-reach population, both groups engage in approximately weekly contact (in-person or by phone) with the research team to continue to verify contact information to promote study retention. At these contact verifications, the research team asks brief questions about self-reported methadone treatment adherence and any changes to treatment enrollment (whether they are still enrolled in methadone treatment as well as any substance use treatment programs outside the study site clinic setting). Participants receive $5 compensation for completing each contact verification visit.

### Power considerations and sample size calculations

2.14

Sample size estimates were calculated using PASS 16.0. Estimates for primary outcomes (retention and number of days in treatment) were calculated assuming: (1) 20% anticipated attrition in patient participation over six months, based on our preliminary work (24); (2) 2-tailed alpha = 0.05; and (3) a 1:1 enrollment ratio. Given prior findings suggesting the proportion of retention in the control group is 0.5 at 180 days, a sample size of 200 (100 patients per group) with an expected retention of 80% at six-month follow-up gives us 80% power to detect a 0.18 proportion difference in retention across conditions. While a binary outcome (retention/attrition) is used in our primary analyses, we can also examine a continuous measure of number of days in treatment. For these models, we would estimate 80% power to detect a small-to-medium effect size (*d* = 0.44).

As recommended in qualitative analysis, the proposed sample sizes for interviews and focus groups are estimates of the number of individuals needed to reach theoretical saturation of responses. The estimates are based on a sample that includes a range of patient, provider/staff and PRSs perspectives. If theoretical saturation is not met with the proposed sample size, we will seek additional approval to increase our sample size.

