##### Quantitative

2.15.1.1

Utilizing a conservative intent-to-treat framework, all participants randomized will be included in analyses. We will examine the baseline equivalence of the groups by comparing participants receiving *Peer Activate* and TAU on sociodemographic characteristics, including sex, age, socioeconomic variables, severity of substance use, and days in treatment. Additional preliminary analyses will be conducted, including evaluating distributional assumptions of variables of interest. We will also examine patterns of missingness across treatment groups to detect deviations from missing at random (MAR) assumptions.

Effectiveness outcomes are evaluated primarily at the six-month follow up as well as at the three-month follow up post baseline. Dichotomous outcomes (including retention defined as retained/not retained at each data point) will be examined using generalized linear mixed modeling (GLMM) which allows for the inclusion of both categorical and continuous predictors as well as correlated observations across time. Two-level, mixed-effects models will be used to examine primary hypotheses. Time points (baseline, post-core follow-up, and final follow-up assessments) are nested within participants. Results will be expressed as either odds ratios (for binary, primary outcomes) or mean differences (for continuous, secondary and exploratory outcomes).

Using standard model-building procedures, treatment condition will be entered as the primary predictor in each model. We will then add additional covariates as indicated by our preliminary analyses, including days in treatment and substance use severity. We will also examine a time by group interaction which, if significant, would indicate that differences between treatment conditions become more or less pronounced across assessment points. *Post hoc* differences between treatment condition at three-month and six-month time points will also be examined using a logit link. To model days in treatment, we will conduct survival analysis using a frailty model to predict lapse in treatment and compare survival curves between treatment conditions, including random effect for PRS. We will assess levels of skew in the days in treatment outcome variable and accommodate our approach accordingly.

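### The stated 80% power for a 0.18 difference in six-month retention does not follow from the section's own inputs: it is about 74% with 100 per arm and 64% with 80 per arm

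*Protocol article*

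**What the plan says.** Section 2.14 (Power considerations and sample size calculations) sets out its assumptions: "20% anticipated attrition in patient participation over six months", "2-tailed alpha = 0.05" and "a 1:1 enrollment ratio". It takes it that "the proportion of retention in the control group is 0.5 at 180 days". With 200 patients, 100 in each group, and 80% retained at the six-month follow-up, it states that this "gives us 80% power to detect a 0.18 proportion difference in retention across conditions". For the continuous measure, number of days in treatment, it adds that "we would estimate 80% power to detect a small-to-medium effect size", given as d = 0.44. The section names the software but not the procedure, and gives no within-person correlation.

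Two other sections bear on which sample size applies. Section 2.12.1.1 defines the primary outcome as one yes/no at about six months, taken from clinical records, with clinic-verified transfers counted as retained. Section 2.15.1.1 (Quantitative) says that "all participants randomized will be included in analyses".

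**The concern.** The section states everything a two-proportion power calculation requires: control proportion, difference, alpha, sidedness, allocation, sample size and attrition. The claimed power can therefore be checked directly, and 0.18 looks too small for 80% power with 100 per arm, more so with 80.

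The effective sample size is also unclear. The 20% allowance is for loss of study participation, but the primary outcome is read from charts and everyone randomized is to be analysed. If the charts are complete, loss of participation costs no primary outcome data and 100 per arm applies. If they are not, it is nearer 80.

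This is the trial's only power statement for its primary outcome. A null result could be read as evidence against a difference of 0.18 with a 20% false-negative risk, when the actual risk is larger.

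**Working it through.** **Inputs (all from section 2.14).** p1 = 0.50; difference 0.18, so p2 = 0.68; two-sided alpha 0.05 (z = 1.960); 80% power (z = 0.8416); n = 100 per arm, or 100 × 0.80 = 80 per arm after 20% attrition. A difference in the other direction (0.32) gives the same power.

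**1. Power for 0.18.** With the pooled-variance normal approximation,

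power = Φ{ [d√n − 1.960·√(2·p̄·(1−p̄))] / √(p1(1−p1) + p2(1−p2)) }, with p̄ = 0.59.

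- √(2 × 0.59 × 0.41) = √0.4838 = 0.6956, and 1.960 × 0.6956 = 1.363
- √(0.25 + 0.2176) = √0.4676 = 0.6838
- n = 100: (1.800 − 1.363)/0.6838 = 0.639, so power = **73.8%**
- n = 80: (1.610 − 1.363)/0.6838 = 0.361, so power = **64.1%**

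**2. Does the choice of test matter?** For 0.50 versus 0.68, two-sided:

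| Method | n = 100 per arm | n = 80 per arm |
|---|---|---|
| Pooled z | 73.8% | 64.1% |
| Unpooled z | 74.9% | 65.3% |
| Arcsine | 74.0% | 64.4% |
| Wald log-odds | 72.9% | 63.3% |
| Chi-square, exact power | 74.6% | 63.3% |
| Continuity-corrected | 68.9% | 57.8% |
| Fisher | 69.7% | 57.2% |

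None exceeds 74.9%, so neither rounding nor the choice of test explains the gap.

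**3. Difference detectable with 80% power from 0.50.** Solving the same formula for d gives **0.193** with 100 per arm and **0.215** with 80 per arm.

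**4. Sample size for 0.18.** n = (1.363 + 0.8416 × 0.6838)² / 0.18² = 1.9388² / 0.0324 = 116.0, which rounds up to 117 evaluable per arm. Allowing for 20% attrition, 117/0.80 = 146.25, or 147 per arm (294 in total).

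**5. The companion figure, d = 0.44.** The normal approximation gives detectable d = (1.960 + 0.8416)·√(2/n).

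- n = 80: 2.8016 × 0.1581 = 0.443 (t-test: 0.446)
- n = 100: 2.8016 × 0.1414 = 0.396 (t-test: 0.398)

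The stated 0.44 therefore reproduces at 80 per arm, where its power is 79.5% (normal) or 79.0% (t). At 100 per arm it would have 87.5% (normal). The continuous figure thus appears to include the attrition, and on that basis the binary figure has 64% power.

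**6. Readings that might recover 0.18.**

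- One-sided test: power 83.1% at n = 100 and 75.2% at n = 80 (detectable differences 0.172 and 0.192). With continuity correction at n = 100 it is 79.2%. The section says two-tailed.
- A different control rate: 0.18 is detectable with 80% power if control retention is about 0.61 (n = 100) or 0.70 (n = 80). The section says 0.5.
- Taking the 80% as intervention-arm retention: 0.62 versus 0.80 gives 80.6% at n = 100, which again contradicts 0.5; 0.50 versus 0.80 gives 99.6%, which is not a difference of 0.18.

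Each of these that comes near the stated figure contradicts a stated input.

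**The case against.** The strongest reply is that the section does not name its procedure, and section 2.15.1.1 plans a two-level generalized linear mixed model with time points nested in participants. A repeated-measures calculation can return about 0.18. Suppose there are two equally informative follow-ups with the same difference at both. If ρ is the correlation between them, the effective sample size is n/[(1 + ρ)/2]. Power for 0.18 is then:

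- at 80 per arm: 82% for ρ = 0.3, 77% for 0.5 and 71% for 0.7;
- at 100 per arm: 90%, 85% and 81% for the same values, and 76% for ρ = 0.9.

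So an undisclosed calculation of this kind may lie behind the number. It does not validate the statement as printed: the correlations and the equal effect at three and six months are assumptions that the article does not make, and the primary outcome is a single six-month yes/no.

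A second reply is that 64% applies only if a fifth of primary outcomes are missing. That is right. With complete charts the shortfall is about 6 points of power, or 0.193 against 0.18. But the section itself attaches the 80% follow-up to the binary figure, so the 80-per-arm reading is a fair one, and the claim fails at 100 per arm too.

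A third reply is that allowing for attrition while planning an intent-to-treat analysis is ordinary caution. As a practice it is. The difficulty is that the allowance appears to have been applied to d, while 0.18 agrees with neither sample size.

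Finally, the error does not bias the treatment estimate or its confidence interval, and a null result is better judged by the interval than by planned power. That limits the harm but does not make the stated figure correct.

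**Conclusion.** The concern holds. From the inputs in section 2.14, power for a 0.18 difference is about 74% if the primary outcome is known for all 100 per arm and about 64% if it is known for 80 per arm. The false-negative risk at 0.18 is therefore 26% to 36%. The differences detectable with 80% power are 0.193 and 0.215. The two effect sizes in the paragraph do not share a sample size: 0.18 needs 117 evaluable per arm, whereas d = 0.44 fits about 80.

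This rests on a single-time-point, two-sided comparison of two proportions with control retention of 0.50, which matches the primary outcome as defined. It would change only if the authors used, and disclosed, a further assumption such as a within-person correlation. The figure must be corrected or explained, because it is the only power statement for the primary outcome.

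**What to change.** Restate section 2.14 without changing enrolment. Suggested wording:

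*With 100 patients per arm and chart-based retention ascertained for all randomized participants, the trial has 80% power to detect a difference of 0.193 (0.50 versus 0.693) at two-sided alpha 0.05; power for a difference of 0.18 is 74%. If the primary outcome were evaluable for only 80 per arm, the detectable difference would be 0.215 and power for 0.18 would be 64%.*

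Say which of the two sample sizes is expected, given that retention comes from clinical records, and use it for days in treatment as well: d = 0.40 with 100 per arm, or 0.45 with 80 per arm (t-test). If the 0.18 came from a repeated-measures calculation, state the procedure, the correlation and the effect assumed at each follow-up instead.

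The cost is wording only. The stated detectable difference becomes slightly less favourable; there are no added patients and no change to endpoint or analysis.

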### Data management and analysis

2.15

The research team developed a study-specific data management protocol and standard operating procedures for data collection, quality control, and data extraction. The PI and research coordinators provide ongoing oversight of data management throughout the study and are responsible for checking the accuracy of collected data on an ongoing basis and again prior to data analysis.

All protected health information (PHI) is stored on secure data storage servers or as paper records in a double-locked location at the University of Maryland campus, to which only authorized research personnel have access. Confidentiality is assured as participants are identified on all study materials by only a participant number and date of visit. All data management activities utilize REDCap (Research Electronic Data Capture), a software toolset and workflow methodology for electronic collection and management of research and clinical trial data (53). REDCap provides secure, web-based applications with an intuitive interface for users to enter data and have real time data checking such as validation rules (with automated data type and range checks) at the time of entry. All data input in REDCap are reviewed by a different research assistant to ensure completion and accuracy of data collection. Data files are downloaded from REDCap database on a weekly basis and saved on the study-designated, secure drive to maintain backup copies of the data. De-identified audio recordings and transcripts are stored on secure, password-protected drives at UMCP.

#### Data analysis

2.15.1

##### Quantitative

2.15.1.1

Utilizing a conservative intent-to-treat framework, all participants randomized will be included in analyses. We will examine the baseline equivalence of the groups by comparing participants receiving *Peer Activate* and TAU on sociodemographic characteristics, including sex, age, socioeconomic variables, severity of substance use, and days in treatment. Additional preliminary analyses will be conducted, including evaluating distributional assumptions of variables of interest. We will also examine patterns of missingness across treatment groups to detect deviations from missing at random (MAR) assumptions.

Effectiveness outcomes are evaluated primarily at the six-month follow up as well as at the three-month follow up post baseline. Dichotomous outcomes (including retention defined as retained/not retained at each data point) will be examined using generalized linear mixed modeling (GLMM) which allows for the inclusion of both categorical and continuous predictors as well as correlated observations across time. Two-level, mixed-effects models will be used to examine primary hypotheses. Time points (baseline, post-core follow-up, and final follow-up assessments) are nested within participants. Results will be expressed as either odds ratios (for binary, primary outcomes) or mean differences (for continuous, secondary and exploratory outcomes).

Using standard model-building procedures, treatment condition will be entered as the primary predictor in each model. We will then add additional covariates as indicated by our preliminary analyses, including days in treatment and substance use severity. We will also examine a time by group interaction which, if significant, would indicate that differences between treatment conditions become more or less pronounced across assessment points. *Post hoc* differences between treatment condition at three-month and six-month time points will also be examined using a logit link. To model days in treatment, we will conduct survival analysis using a frailty model to predict lapse in treatment and compare survival curves between treatment conditions, including random effect for PRS. We will assess levels of skew in the days in treatment outcome variable and accommodate our approach accordingly.

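### For PHQ-8, and possibly Timeline Followback, the plan does not fix which mean difference is the result, and names no baseline-score adjustment although baseline appears to be an outcome time point

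*Protocol article*

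**What the plan says.** All modelling text is in section 2.15.1.1 (Quantitative) of the Protocol article.

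- **Model structure:** "Two-level, mixed-effects models will be used to examine primary hypotheses", and "Time points (baseline, post-core follow-up, and final follow-up assessments) are nested within participants".
- **Predictor:** "treatment condition will be entered as the primary predictor in each model".
- **Reported quantity:** odds ratios for the binary outcomes, and "mean differences (for continuous, secondary and exploratory outcomes"). No time point or contrast is attached to the mean difference.
- **Covariates:** "We will then add additional covariates as indicated by our preliminary analyses, including days in treatment and substance use severity". The same section lists "socioeconomic variables, severity of substance use, and days in treatment" among the characteristics compared between arms at baseline.
- **Other contrasts:** "We will also examine a time by group interaction which, if significant, would indicate that differences between treatment conditions become more or less pronounced". Post hoc comparisons at three and six months are planned, with a logit link.
- **Timing:** effectiveness is to be judged mainly at six months, and also at three.

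Section 2.12.2 (Secondary outcomes) lists "changes in substance use over six months using both urinalysis and timeline follow back methods and depressive symptoms using the PHQ-8". Table 1 shows PHQ-8 collected at baseline, post-core follow-up and final follow-up.

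**The concern.** Baseline is measured before randomization, so the expected difference between arms at that visit is zero. If baseline is one of the outcome rows, a single treatment coefficient averages that zero with the follow-up effects and moves toward the null. It also carries any chance baseline imbalance with it.

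The time-by-group term avoids this because it targets change from baseline. It does not, however, use the baseline score as efficiently as adjustment does. The three- and six-month comparisons could have settled the matter, but a logit link does not give a mean difference for a continuous score.

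The article therefore leaves more than one candidate for the mean difference, and none is stated to be both the six-month effect and adjusted for baseline. At stake is the trial's statement on depression, which the Conclusion puts forward as something the trial will inform, and possibly its statement on substance use. A real benefit could be understated or missed, or the contrast could be chosen after the data are seen.

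**Working it through.** **Inputs from section 2.14 (Power considerations):** 100 per arm with 20% attrition, so 80 per arm; two-sided alpha 0.05; d = 0.44 with 80% power. The d is stated for days in treatment and is borrowed here only as an illustration. No power is claimed for PHQ-8 or Timeline Followback.

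**Assumptions not in the article:** outcome SD 1, equal correlation ρ between any two visits (0.3, 0.5 and 0.7 tried), and the same effect at both follow-ups.

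**Step 1. Reproduce the plan's figure.** k = 0.44 × √(80/2) = 2.78. Power = Φ(2.78 − 1.96) = 0.795 (0.790 by t-test). This agrees with the stated 80%.

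**Step 2. Expected value of a pooled treatment main effect.** Over baseline and two follow-ups: (0 + 0.44 + 0.44)/3 = 0.293, which is two thirds of 0.44.

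**Step 3. Power of three possible mean differences.** In each case power = Φ(z − 1.96).

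- Main effect over three rows: z = k × (2/3) / √((1 + 2ρ)/3)
- Change from baseline to six months (time-by-group): z = k / √(2(1 − ρ))
- Six-month difference adjusted for baseline: z = k / √(1 − ρ²)

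At ρ = 0.5:

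- Main effect: z = 2.78 × 0.667/0.816 = 2.27
- Change: z = 2.78/1 = 2.78
- Adjusted: z = 2.78/0.866 = 3.21

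| ρ | Main effect | Change contrast | Baseline-adjusted | Adjusted minus change |
|---|---|---|---|---|
| 0.3 | 71.9% | 65.2% | 83.1% | 17.9 points |
| 0.5 | 62.3% | 79.5% | 89.5% | 10.0 points |
| 0.7 | 54.5% | 94.9% | 97.4% | 2.5 points |

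**Step 4. Simulation check.** 200 trials were simulated with 100 per arm, 20% with no follow-up, ρ = 0.5 and a true effect of 0.44.

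- The pooled main effect averaged 0.253. This is below 0.293 because participants without follow-up still contribute baseline rows.
- The time-by-group term at six months averaged 0.437 with standard error 0.154, so it is not diluted.
- A model that keeps the baseline row but holds the arm means equal there also averaged 0.437 at six months, with standard error 0.137. The closed form for baseline adjustment gives the same standard error: √(2/80 × 0.75) = 0.137.

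The last two results show that a baseline row does not in itself cost precision. The loss comes from leaving the baseline arm means unconstrained and the baseline score unadjusted.

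**The case against.** The strongest reply is that a condensed article is being read as if it fixed a secondary-outcome model. The two-level sentence speaks of the primary hypotheses, and no sentence in section 2.15.1.1 names PHQ-8 or Timeline Followback. The same section judges effectiveness mainly at six months, and both section 2.12.2 and Table 1 speak of changes. That points to time-specific or change contrasts, not an average that includes baseline. The exact contrast for a secondary outcome is often left to an analysis plan.

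Much of this stands. Applying the model to PHQ-8 is an inference. It is supported by the statement that treatment is the main predictor in each model, by the mention of mean differences for continuous secondary outcomes, and by the absence of any other model for them. The six-month emphasis makes a pooled main effect less likely, but nothing in the section rules it out.

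Three stronger readings are tempting and are not supported:

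- **That the baseline score is never a covariate.** The covariate list is open, and substance use severity is on it. Its measure is not stated, so it could be baseline Timeline Followback. For PHQ-8 one can say only that no baseline covariate is named.
- **That the mean difference is diluted.** This holds only if the pooled main effect is what gets reported. The planned time-by-group term is undiluted and subtracts any baseline imbalance.
- **That dilution for Timeline Followback reaches one half.** This would need a single follow-up. It rests on a Table 1 row in which two measures run together and which may be broken, while section 2.12.2 refers to six months.

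The reply does not remove the point that the modelling choices the article does state leave the continuous result open between contrasts of different meaning and precision.

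**Conclusion.** The point holds in a limited form. The article appears to place baseline among the outcome time points for PHQ-8, and possibly for Timeline Followback. It makes treatment condition the main predictor, names no baseline PHQ-8 covariate, and does not identify the contrast behind the mean difference.

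The size depends on which contrast is meant. A pooled main effect would estimate about two thirds of a constant follow-up effect. A time-by-group contrast would be unbiased, but would give up 10 points of power against baseline adjustment at ρ = 0.5, about 18 at 0.3 and about 2.5 at 0.7. These figures rest on an assumed correlation, equal correlation between visits, a constant effect and a borrowed d of 0.44, so they show direction and order of magnitude only.

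The change is worth making because it is nearly free. It concerns secondary outcomes and leaves the primary retention conclusion untouched.

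**What to change.** State in section 2.15.1.1 that for PHQ-8 and Timeline Followback the reported effect is the between-arm mean difference at six months, with three months as supportive. It should come from a model with treatment, visit and treatment-by-visit, in one of two forms:

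- follow-up visits only as outcome rows, with the participant's own baseline value of that outcome as a pre-specified covariate; or
- the baseline row kept, with arm means constrained equal at baseline.

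The baseline adjustment should not depend on what the preliminary analyses show. State separately that the logit-link contrasts apply to the binary outcomes.

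The cost is a few sentences. Baseline values are already collected, so no patients or visits are added. The downside is one extra parameter in the covariate form and a rule for any missing baseline scores.
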